## Abstract

**Introduction::**

Subacromial impingement syndrome (SIS) is one of the most common diseases inducing shoulder pain. Acupuncture is a source of pain relief that has been used for SIS; however, there is no clinical study about image-guided acupuncture for SIS. The aim of this study is to evaluate the effectiveness and safety of fluoroscopy-guided acupuncture in patients with SIS.

**Methods::**

This is the protocol for a randomized, patient-assessor blind, parallel clinical trial comparing fluoroscopy-guided acupuncture to acupuncture without fluoroscopy. There will be a 1-week run-in period before random allocation to 2 groups. The total duration of the clinical trial will be 3 weeks including 2 weeks for the follow-up period. A total of 57 participants will be enrolled for the clinical trial. Acupuncture will be conducted in 2 sessions for each group, once at baseline and once at the 1-week mark. The primary outcome will be 100 mm pain visual analogue scale. Secondary outcomes will include the Neer and Hawkins test, the Modified Constant Murley Score scale, the Shoulder Pain And Disability Index, the patient satisfaction degree, and the accuracy rate of acupuncture. For the evaluation of safety, adverse events will be monitored.

**Discussion::**

We designed the clinical trial using image-guided acupuncture. This will be the first trial to study the effectiveness of image-guided acupuncture for SIS compared with acupuncture using the proportional measurements.

**Trial registration::**

Clinical Research Information Service Registration Number is KCT0002751. Registered on March 23, 2018.

## Introduction

1

Subacromial impingement syndrome (SIS) is one of the most common causes of shoulder pain and can cause rotator cuff tendinitis.^[1,2]^ SIS is caused by narrowing of the subacromial space due to various causes, and it can result in shoulder pain, limitation of movement, and loss of strength.^[3,4]^

Currently, treatments of SIS include medications such as analgesic agents, conservative therapies such as exercise and physical therapy, and injection therapy.^[5]^ If conservative therapies fail, steroid injections are most commonly used as the next line of therapy.^[6]^

Acupuncture is an effective treatment for chronic pain such as back pain, knee pain, lumbar pain, and shoulder pain.^[7]^ For shoulder pain, acupuncture has the effects of pain relief, improvement of range of motion, and improvement of shoulder function, and these effects are sustained for up to 6 months, suggesting a long-term effect.^[8]^ In the previous study about SIS, acupuncture and exercise therapy was shown to be effective in improving shoulder function over 12 months.^[9]^

Because the subacromial space is anatomically narrow, it is difficult to inject into the space accurately.^[10]^ Conventional acupuncture treatment, which determines the depth of acupuncture based on the proportional measurements without the aid of imaging devices, may be more difficult to insert needles into the exact target space.

In this study, we would like to use the portable fluoroscopic X-ray system (PF-X-ray, MX-DRF0815, Nano Focus Ray, Republic of Korea) to guide acupuncture into the subacromial space. Because fluoroscopy can guide the bones better than the ultrasound guide used for soft tissues, it is effective for guiding insertion into the narrow acupoint space between the acromion and the humerus.

We designed this study protocol to evaluate the effects and the safety of fluoroscopy-guided acupuncture for SIS, compared with acupuncture without fluoroscopy.

## Methods and design

2

### Study design and ethics approval

2.1

This study will be a randomized, patient-assessor blind, controlled clinical trial with 2 parallel groups. The protocol of this study has been approved by the institutional review board (IRB) of Wonkwang University Gwangju Hospital (WKIRB-2017/13) on October 28, 2017. This trial study will be conducted in Wonkwang University Gwangju Hospital in Korea according to the ethical principles of the “Helsinki Declaration.” We will make a poster and advertise it to recruit participants. Before screening for participating in this trial, participants will receive information about the trial. Researchers will proceed with the trial after obtaining a voluntary signature consent, and any identifiable records will be kept confidential. Recruited participants will be randomly assigned to 2 groups: acupuncture treatment with fluoroscopy-guided implementation and acupuncture treatment with proportional measurements. There is a 1-week run-in period before randomization, and total study periods will be 3 weeks, including a 2-week follow-up period. Participants will receive 2 sessions of acupuncture treatment: at baseline (visit 2) and 1 week later (visit 3) (Fig. 1).

**Figure 1 F1:**
[figure not shown]
Flow of the study.

### Inclusion and exclusion criteria

2.2

Inclusion criteria for enrollment are described as follows: males or females aged 25 to 65 years old, with no limitation of range of shoulder motion; those who can be diagnosed as SIS by excluding fracture, dislocation, degenerative arthropathy, os acromiale, subacromial spur, and calcific tendinitis in plain radiography; those with shoulder pain lasting more than 2 months from the onset, the pain is worse when sleeping sideways or lifting the arm over the head, with positive on the Neer or Hawkins test, with more than 50 mm on pain of visual analogue scale (VAS); those who are able to communicate sufficiently with the researcher and complete a questionnaire with minimal help; those who have pledged not to receive treatment other than the prescribed treatment within the period of study; those who agree with written informed consent voluntarily.

Exclusion criteria are described as follows: those who have trauma history of shoulder surgery, fracture, dislocation; those with disorders of the cervical spine or upper extremity that have a significant impact on the shoulder; those who have received injection treatment on the shoulder within the past 6 months; patients with fracture, dislocation, degenerative arthropathy of the glenohumeral joint or acromioclavicular joint, os acromiale, subacromial spur and calcific tendinitis of the shoulder in plain radiography; those with positive findings in a physical examination (drop arm test, empty can test) for exclusion of rotator cuff tear; those with positive findings in the Yergason test for exclusion of biceps tendinitis; those who have been diagnosed with a frozen shoulder (adhesive capsulitis) in a range of motion test; those with pacemaker insertion or significant arrhythmia on electrocardiography); pregnant or breastfeeding females with positive findings in the urine pregnancy test before random assignment, or those who are unable or unwilling to use contraceptive methods (hormonal contraceptives, condoms, intrauterine devices, etc.) to avoid pregnancy throughout the entire study period; those with mental disorders who cannot follow the study protocol; those who were considered as unsuitable for participation by the researcher.

#### Drop out and early termination

2.2.1

When there is a severe adverse event from the subject or a requirement of suspension, trials can be terminated early, and blinding will be released. In the case of a violation of crucial trial plan or by the researcher's judgement, the subject can be dropped from the study. All data and treatment for the drop out will be recorded in case report form.

#### Concomitant treatment

2.2.2

A low dose of aspirin (maximum 200 mg per day) for the prevention of stroke is acceptable. Other concomitant treatments that took place 4 weeks or more before enrollment are also acceptable when the researcher judges that the trial results cannot be affected by them.

Any analgesics for pain relief, muscle relaxants, antidepressants, and anticonvulsants are prohibited. However, use of such analgesics can be acceptable if the subject stopped taking the medicine 1 week before the trial. The same standard applies to physical therapy, injection, and treatments performed by other hospitals for pain relief.

### Randomization and blinding

2.3

Subjects who satisfy all criteria will be assigned a random number using opaque sealed envelopes. The random number sequence is generated by SAS ver.9.0 for Microsoft Windows (SAS Institute Inc, Cary, NC) in a 1:1 ratio. The random number generation and the storage of the envelopes will be independently managed by a third researcher. Neither assessors nor subjects will know the assigned group and the random assignment shall not be known to both until the study is terminated. For blinding, the practitioner should perform only the treatment session and minimize the conversation with subjects. The assessors will perform evaluations independently.

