### Interventions

2.4

Enrolled subjects will receive total of 2 treatment sessions of acupuncture. Time points and details of treatment are as shown in Table 1. Information about the acupuncture treatment details based on the Standards for Reporting Interventions in Clinical Trials of Acupuncture is described in Table 2. After the completion of each treatment session, the experimental group and the control group will be evaluated for the position of the acupuncture using the PF-X-ray and the accuracy of the acupuncture will be evaluated as a success or failure.

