#### Experimental group

2.4.1

Subjects in the experimental group will receive acupuncture treatments to the subacromial space with a fluoroscopy guide. The acupuncture points will be LI15, TE14, and LI16 on the side of the affected shoulder. Acupuncture treatment will be performed for 15 minutes with needle manipulations. We will use disposable sterile acupuncture (0.40 × 50 mm, Dongbang, Republic of Korea). For the acupuncture guide, we will use the PF-X-ray. Before the acupuncture needles are inserted, the shoulder anteriorposterior (AP) view is taken in radiography mode to confirm the subacromial space (however, it may be omitted depending on the patient's condition). We will perform acupuncture treatments with a PF-X-ray guide in fluoroscopy mode.

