#### Control group

2.4.2

Subjects in the control group will receive acupuncture treatments with proportional measurements not using fluoroscopy. Acupuncture points are same as those for experimental group and the locations and depths of acupuncture points will be according to the Korean Medicine Convergence Research Information Center (KMCRIC) standard acupuncture point guideline and proportional measurements.

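### Subjects are said to be blind, but fluoroscopy during needling is described for the experimental arm only, and the one stated session measure does not mask it

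*Protocol article*

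**What the plan says.** The protocol article claims blinding of both parties. Section 2.1: "This study will be a randomized, patient-assessor blind, controlled clinical trial with 2 parallel groups". Section 2.3: "Neither assessors nor subjects will know the assigned group". The measure offered in support is also in section 2.3: "For blinding, the practitioner should perform only the treatment session and minimize the conversation with subjects". Assessors are to evaluate independently.

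The procedures in the two arms differ:

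- Experimental arm (2.4.1): "We will perform acupuncture treatments with a PF-X-ray guide in fluoroscopy mode". A radiograph comes first: "Before the acupuncture needles are inserted, the shoulder anteriorposterior (AP) view is taken in radiography mode to confirm the subacromial space". That step is optional, since "it may be omitted depending on the patient's condition".
- Control arm (2.4.2): "Subjects in the control group will receive acupuncture treatments with proportional measurements not using fluoroscopy". The acupuncture points are the same as in the experimental arm.
- Both arms (2.4): "After the completion of each treatment session, the experimental group and the control group will be evaluated for the position" of the needle, using the same portable X-ray unit.

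The primary outcome (2.5.1) is a 100 mm pain VAS that the subject completes at visits 2, 3 and 4. Section 2.7 bases the primary comparison on the change from visit 2 to visit 3. Treatment is given at visits 2 and 3 (2.1).

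**The concern.** The blinding claim and the treatment descriptions do not fit together as written. An X-ray unit working over the shoulder while needles go in is something the patient may well notice. In the text shown, it happens in one arm only. Keeping conversation short limits what the practitioner may disclose in words, but it does nothing about this difference.

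The primary outcome is the patient's own rating, so independent assessors cannot protect it. SPADI and patient satisfaction (2.5.2), as far as they rest on the patient's own report, are exposed in the same way. The trial asks whether guidance adds benefit to needling at the same points. Any expectation attached to visible imaging falls on exactly that contrast and would be read as benefit of guidance.

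**Working it through.** **1. What a patient meets in each arm, from sections 2.4, 2.4.1 and 2.4.2**

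| Stage of session | Experimental | Control |
|---|---|---|
| Before insertion | AP radiograph, may be omitted | None described |
| During insertion | Fluoroscopy | No fluoroscopy |
| After the session | X-ray position check | X-ray position check |

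The last row is the same in both arms, so having met the device does not identify the arm. The first row differs only when the radiograph is taken. The middle row is the constant difference, and it occurs at both sessions. The measure in section 2.3 acts on none of the three rows.

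**2. Exposure at the primary time point**

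The first arm-specific session is at visit 2 and the second at visit 3. If the visit 3 VAS is taken before needling that day, the patient has had one such session; if after, two. In neither case is the number zero.

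**3. The plan's own sample size, as a check on the inputs (section 2.6)**

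Inputs: difference 2 points, SD 2.3 points, 80% power, significance level 0.05 taken as two-sided, 1:1 allocation.

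n per group = 2 × (1.960 + 0.842)² × 2.3² / 2² = 2 × 7.849 × 5.29 / 4 = 20.8, so 21 per group and 42 in total.

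With 20% dropout: 21 / 0.8 = 26.25, so 27 per group and 54 in total.

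Both figures match section 2.6.

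**4. What an expectation bias would do (illustration)**

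Assume no true effect of guidance and a shift of b mm in favour of the guided arm, due only to expectation. The values of b are assumptions; the documents give none. The SD of 2.3 points is read as 23 mm on the 100 mm scale and applied to the change score.

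Standard error = 23 × √(2/n). Non-centrality = b / standard error. The rejection rate is the probability that a non-central t variable on 2n − 2 degrees of freedom falls outside the two-sided 0.05 limits.

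- n = 21: standard error 7.10 mm, 40 degrees of freedom, limits ±2.021.
- n = 27: standard error 6.26 mm, 52 degrees of freedom, limits ±2.007.

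| Assumed bias b | Non-centrality, n = 21 | Rejection, n = 21 | Non-centrality, n = 27 | Rejection, n = 27 |
|---|---|---|---|---|
| 0 mm | 0 | 5.0% | 0 | 5.0% |
| 5 mm | 0.70 | 10.6% | 0.80 | 12.3% |
| 8 mm | 1.13 | 19.6% | 1.28 | 24.1% |
| 10 mm | 1.41 | 28.0% | 1.60 | 34.8% |

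The column for 21 per group is the more relevant one. It is the number expected to remain after dropout, and section 2.7 makes the per-protocol set the main set. The column for 27 applies only if every enrolled patient is analysed.

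**The case against.** The strongest reply is that this is a condensed article. Section 2.4 sends the treatment details to Tables 1 and 2, which are not shown, and the full protocol is not at hand. Any of these could describe a dummy set-up. Saying that controls are needled without fluoroscopy does not say that the unit is out of the room or left unpositioned. This stands as a limit on the conclusion: it cannot be said that no masking exists. It does not remove the point, because the article does name a measure taken for the sake of blinding, and that measure leaves the visible difference untouched.

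A second reply is that the position check in both arms partly protects blinding, since controls also meet the device and each patient sees only one sequence. This also stands. It narrows the cue to timing but does not equalise what happens during insertion.

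A reader might go further and infer that patients know fluoroscopy is what separates the arms, and so know their allocation. The documents do not support this. Section 2.1 says only that participants are informed about the trial before screening, and the consent text is not shown. Nor is a pre-insertion radiograph a fixed feature of the experimental arm.

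Finally, the bias sizes have no anchor in the documents, and that is conceded.

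**Conclusion.** The point holds in a limited form. The article asserts that subjects are blind, and the procedures it describes would not by themselves deliver this: fluoroscopy during insertion is given for one arm, and the stated measure does not conceal it. That patients infer their arm is plausible, not documented, and depends on what they are told and on whether an undescribed dummy procedure exists.

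If expectation did favour the guided arm by an assumed 5 to 10 mm, the chance of a false positive primary result would rise from 5% to between about 11% and 28% with 21 per group (12% to 35% with 27). These figures show sensitivity and do not estimate the actual bias. The table should not be read as evidence that a bias of this size will occur. The text should be changed before the result is presented as patient-blind.

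**What to change.** In section 2.4.2, if a dummy procedure already exists, state it; one sentence would be enough. If none exists, position the portable X-ray unit over the shoulder during control needling, with exposure off, for a time similar to that in the experimental arm. Keep the monitor out of the patient's view in both arms.

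If neither is possible, describe the trial as assessor-blind only in the abstract and in sections 2.1 and 2.3, and interpret the self-rated outcomes accordingly.

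Optionally, add one case report form question at visit 4, after outcomes are recorded, asking which arm the patient believes they were in. This measures blinding but does not create it, and its absence is not an error in the plan.

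The cost is a few extra minutes per control session, with no added radiation or staff.

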### Interventions

2.4

Enrolled subjects will receive total of 2 treatment sessions of acupuncture. Time points and details of treatment are as shown in Table 1. Information about the acupuncture treatment details based on the Standards for Reporting Interventions in Clinical Trials of Acupuncture is described in Table 2. After the completion of each treatment session, the experimental group and the control group will be evaluated for the position of the acupuncture using the PF-X-ray and the accuracy of the acupuncture will be evaluated as a success or failure.

**Table 1 T1:**
[figure not shown]
Progress table of clinical trial.

**Table 2 T2:**
[figure not shown]
STRICTA.

#### Experimental group

2.4.1

Subjects in the experimental group will receive acupuncture treatments to the subacromial space with a fluoroscopy guide. The acupuncture points will be LI15, TE14, and LI16 on the side of the affected shoulder. Acupuncture treatment will be performed for 15 minutes with needle manipulations. We will use disposable sterile acupuncture (0.40 × 50 mm, Dongbang, Republic of Korea). For the acupuncture guide, we will use the PF-X-ray. Before the acupuncture needles are inserted, the shoulder anteriorposterior (AP) view is taken in radiography mode to confirm the subacromial space (however, it may be omitted depending on the patient's condition). We will perform acupuncture treatments with a PF-X-ray guide in fluoroscopy mode.

#### Control group

2.4.2

Subjects in the control group will receive acupuncture treatments with proportional measurements not using fluoroscopy. Acupuncture points are same as those for experimental group and the locations and depths of acupuncture points will be according to the Korean Medicine Convergence Research Information Center (KMCRIC) standard acupuncture point guideline and proportional measurements.

### Outcomes

2.5

#### Primary outcome

2.5.1

The primary outcome will be the change 100 mm pain VAS for shoulder pain. For rating severity of shoulder pain intensity, 100 mm pain VAS will be assessed by the subjects self-checking and evaluating the degree of pain using the 100 mm line, which is described at one end as “no pain” and at the other end as “worst pain imaginable.” This outcome will be measured at visits 2, 3, and 4. At each measurement, the shoulder pain intensity that occurs during the Neer Test and the Hawkins Test will be measured.^[11]^

#### Secondary outcomes

2.5.2

The secondary outcomes will be the tests for impingement sign and function of the shoulder joint. These will be measured at visits 2, 3, and 4. To assess improvement of impingement syndrome, we will perform the Neer test and Hawkins test.^[11]^ Function of the shoulder joint will be assessed by the Modified Constant Murley Score scale (Modified CMS) and the Shoulder Pain And Disability Index (SPADI). We will also evaluate the patient satisfaction degree and accuracy rate of acupuncture. Using the PF-X-ray, we will check the shoulder standard AP view and scapular Y view. We will rate the procedure as a success when the acupuncture needle is accurately inserted into the subacromial space.

#### Safety evaluation

2.5.3

We will check the vital sign at every visit. We will check for the adverse events (AEs) and serious adverse events (SAEs) at every visit of the study. For AEs and SAEs, we will record the onset date, end date, the intensity, the relationship with the clinical trial, the result, and the action taken to address the AE. When the SAE occurs, we will take an appropriate measure to minimize adverse reactions and report to the IRB within the period set by the IRB.

### Sample size

2.6

For calculating the sample size, we searched for a clinically significant difference of VAS in previous studies. There was no previous study with the same experimental and control groups as ours evaluating the efficacy with the VAS as a primary outcome. So referring to the previous clinical trial, which included a broad population of patients with various musculoskeletal conditions, we determined a significant difference of VAS as 2 point.^[12–14]^ From the study comparing fluoroscopically guided and blind corticosteroid injections, standard deviation was conservatively assumed to be 2.3.^[15]^ We calculated the sample size with 80% power at a significance level of 0.05. The sample size is 42 in total and 21 for each group. Assuming a dropout of about 20%, about 54 patients in total (27 per each group) may be needed.

### Statistical analysis

2.7

For statistical analysis, a full analysis set (FAS), per-protocol set (PPS), and the safety set will be used. Both the FAS analysis and the PPS analysis will be used for the efficacy evaluation. PPS will be the main set according to the principle of intentionality treatment.

Evaluation of the primary outcome will be conducted by VAS change after 2 treatment sessions (visit 3) compared with baseline (visit 2). To compare 2 groups, 2-sample *t* test will be used. The paired *t* test will be used for analysis in each group. For the interaction of treatment over time, repeated measures analysis of variance will be used. And secondary outcomes (modified CMS and SPADI) are evaluated by the same methods as the primary outcome. The Neer test and Hawkins test will be summarized as frequency and percentage, and the comparison between the 2 groups will be performed using the *χ*^2^ test or the Fisher exact test. The accuracy ratio acupuncture is calculated by comparing the ratio between the 2 groups.

For safety evaluation, a 2-sample *t* test or Mann–Whitney *U* test will be conducted in case of continuous variable, and *χ*^2^ test or Fisher exact test will be conducted for assessing the differences of incidence of adverse events.

In the case of missing data, the method of last observation carried forward (LOCF) will be performed.

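### The per-protocol set is named the main efficacy set on intention-to-treat grounds, so the primary comparison would rest on exclusions made after randomisation

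*Protocol article*

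**What the plan says.** Section 2.7 (Statistical analysis) names a FAS, a PPS and a safety set. On efficacy it says "Both the FAS analysis and the PPS analysis will be used for the efficacy evaluation", and then ranks the two: "PPS will be the main set according to the principle of intentionality treatment". The last words of that sentence evidently mean intention-to-treat. For the primary outcome, the change in pain VAS, it says "To compare 2 groups, 2-sample *t* test will be used". On missing values it says "In the case of missing data, the method of last observation carried forward (LOCF) will be performed".

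Section 2.2.1 (Drop out and early termination) gives the grounds for removing someone: "In the case of a violation of crucial trial plan or by the researcher's judgement, the subject can be dropped from the study". Section 2.3 (Randomization and blinding) says "Neither assessors nor subjects will know the assigned group". It does not list the practitioner as blinded, and no section says who decides on a drop or whether that person is blinded.

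**The concern.** The stated set and the stated reason for it are incompatible. Intention-to-treat keeps every randomised patient in the group assigned. A PPS removes patients for what happens after randomisation.

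In a trial that looks for a difference, a leading PPS gives up the protection of randomisation for the main result. Two features make this more than a formality:

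- **Grounds for exclusion.** They are partly discretionary. The rules in Sections 2.2 and 2.2.2 against other treatment and analgesics are also ones that patients with persisting pain are the more likely to break. Violations may therefore be related to outcome.
- **Size and outcome.** The trial needs 42 evaluable patients and its primary outcome is self-rated. A few selective exclusions can change the conclusion, in favour of either arm.

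A leading PPS also sidelines the planned LOCF, which would then serve mainly the secondary FAS analysis.

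**Working it through.** **1. The passages side by side**

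| Place | Content | Points to |
|---|---|---|
| 2.7, set named | PPS is the main set | Analysis of a subset selected after randomisation |
| 2.7, reason given | Intention-to-treat | FAS |
| 2.1, 2.6, 2.7, design | Two parallel groups, 2-point VAS difference, two-sample *t* test, no margin | Difference trial, so FAS |
| 2.2.1, drops | Crucial violation or researcher's judgement | Exclusions that may depend on arm or response |

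Only the set named in 2.7 points to the PPS. The reason given and the design both point to the FAS.

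**2. The plan's sample size**

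Inputs from Section 2.6: difference 2, SD 2.3, alpha 0.05 (taken as two-sided), power 80%, dropout about 20%.

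- n per arm = 2 × (1.960 + 0.842)² × 2.3² / 2² = 20.8, so 21 per arm and 42 in total.
- 21 / (1 − 0.20) = 26.25, so 27 per arm and 54 in total.

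Both match the plan. Choosing the FAS as main set does not alter them. By the normal approximation, power is 89% with all 27 per arm analysed (complete data, effect undiluted) and 80% with 21 per arm.

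**3. What selective exclusion could do**

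Assumptions: no true difference; normal outcome; SD 23 mm (the plan's 2.3 points read on the 100 mm scale); 27 per arm; two-sided *t* test at 0.05; simulated trials. With nobody excluded, the type I error is about 5%. Each cell gives bias / type I error when k patients are excluded.

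| k | A: k poorest from one arm, none from the other | B: k poorest from one arm, k at random from the other | C: k at random from the lower half of one arm, k at random from the other |
|---|---|---|---|
| 1 | 1.7 mm / 6.5% | 1.7 mm / 6.5% | 0.7 mm / 5.1% |
| 2 | 3.3 mm / 9.4% | 3.3 mm / 9.1% | 1.5 mm / 5.4% |
| 3 | 4.6 mm / 12.8% | 4.6 mm / 12.9% | 2.3 mm / 5.9% |
| 5 | 7.3 mm / 23.2% | 7.2 mm / 22.0% | 4.2 mm / 8.5% |

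A is based on 100,000 trials; B and C on 40,000 each. In a fourth case, the 5 poorest leave both arms: bias is about 0 and the type I error about 10%, because trimming shrinks the estimated variance.

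For scale, 20% of 27 is about 5 patients per arm. That is the plan's allowance for dropout in both arms; it is not a forecast that the 5 poorest responders leave one arm.

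**The case against.** The strongest reply is that the sentence may be a slip. Since its reason is intention-to-treat, PPS may have been written for FAS, and then no claim would rest on the PPS. This is possible, but the text as it stands still fixes the wrong set, and the correction is the same on either reading.

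Other points stand in part:

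- **Bias route.** It is inferred. The article does not say that the unblinded practitioner decides on drops, and Section 2.3 confines that person to giving treatment. Arm-dependent exclusion is therefore possible, not shown. But nothing requires the person deciding to be blinded.
- **PPS membership.** The article does not define it. That subjects dropped under 2.2.1 leave the PPS is the natural reading, not an explicit statement. Superiority is likewise inferred from the test and the absence of a margin.
- **Size.** Columns A and B are worst cases. The fair range of type I error is about 5% to 23%, depending on how selective the exclusions are.
- **FAS already planned.** A disagreement between the sets would be visible, but the protocol says that the PPS result then leads.
- **Imputation.** A FAS-led analysis is not free of assumptions. For a patient with no VAS after baseline, LOCF carries the baseline forward and gives a change of zero. This is a reason to keep collecting data, not a reason to let the PPS lead.

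**Conclusion.** The concern holds. The designation of the main efficacy set in Section 2.7 is wrong as written, whether by slip or by intent, and nothing in the article supports a leading PPS. This does not depend on the simulation.

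The possible harm runs from almost nothing, if exclusions are nearly unrelated to outcome, to a bias of about 7 mm and a type I error of about 23%, if the 5 poorest responders leave one arm. For comparison, the trial is powered for a difference of 2 points, or 20 mm on the same reading of the scale. These figures assume normal data, an SD of 23 mm and 27 per arm; they are an illustration, not a prediction.

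The point must be settled before outcome data are seen. Choosing between the sets afterwards would look driven by the results.

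**What to change.** Replace the sentence in Section 2.7 with: *The FAS (all randomised patients, analysed in the group assigned) is the primary analysis set according to the intention-to-treat principle; the PPS analysis is supportive.*

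Add to Section 2.2.1 that patients dropped from the study stay in the FAS and that their visit 3 and visit 4 outcomes are collected where possible. That limits how much the primary result leans on LOCF. It would also help to define PPS exclusions in advance and have them decided without knowledge of the group.

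The core change is one sentence. Both analyses are already planned, and 21 evaluable and 27 enrolled per arm stand as stated. The only added effort is follow-up of dropped patients at the remaining visits.
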